### Trial design {8}

This study is a phase II, triple-blind, 1:1 drug:placebo allocation, parallel-arm, randomized, placebo-controlled trial under an investigational new drug (IND) application to the US FDA. The trial is registered with ClinicalTrials.gov (NCT04590508).

## Methods: participants, interventions, and outcomes

### Study setting {9}

Clinical visits and specimen preparation will be conducted at the National University of Natural Medicine (NUNM) Helfgott Research Institute in Portland, OR.

### Eligibility criteria {10}

Eligibility criteria are delineated in Table 2. Delineation of procedure flow and study visit descriptions can be found in Fig. 1 and Table 3, respectively. Candidates who meet modifiable exclusion criteria (e.g., taking prohibited dietary supplements) will be given the option to “wash out” for 14 days and re-contact the study team.

**Table 2 Tab2:** Participant eligibility

Inclusion criteria	Exclusion criteria
• Adults 21–70 years of age • Active Crohn’s disease not in remission based on a CDAI score >150 • Willing to take isolated XN as a dietary supplement for 8 weeks • Willing to have blood drawn biweekly and fast for 10–12 h before blood draws • Willing and able to collect biweekly stool samples at home • Willing and able to collect a 24-h urine sample before each study visit • Able to speak, read, and understand English • Able to provide written informed consent • Non-smokers (including tobacco and Cannabis products in any delivery including cannabidiol) • For individuals of child-bearing potential, willing to use an intrauterine device or two other concurrent forms of birth control to prevent pregnancy while enrolled	• Variable dosing of anti-inflammatory medications >1×/week • Currently or recent (within last 14 days): o Taking any dietary supplements containing xanthohumol, flavonoids, or other “anti-inflammatories” including curcumin, turmeric, fenugreek, hops, rosemary, ginger, white willow, devil’s claw, fish oil (doses >1 g/day), or quercetin o Receiving intravenous nutrition support therapy o Taking anti-coagulant or anti-platelet prescription medications o Taking antibiotic, antiparasitic, or antifungal medications orally or intravenously o Initiated of or changes to supplements or medications o Initiated or changes to an exercise regimen o Initiated changes to a food plan o Involvement of a significant diet, weight loss, or very low-calorie liquid diet programs o Use of illicit drugs/substances o Participation in an interventional research study • Consumption of more than 1 beer per day or typical intake of more than 2 alcohol-containing beverages per day, more than 14 per week, or more than 4 in any single day within the past 14 days • Hospitalization (for any reason other than a scheduled medical procedure) within the last 3 months • Gastrointestinal surgery within the last 3 months • Malignancy within the last 5 years (except basal cell carcinoma, squamous cell carcinoma, and/or carcinoma in situ of the cervix) • Women who are lactating, pregnant, or planning pregnancy within the next 4 months • Do not have an active primary care provider or specialist (i.e., gastroenterologist) managing their CD

**Fig. 1 Fig1:**
[figure not shown]
Flow of participation

**Table 3 Tab3:**
[figure not shown]
Study procedures

*CDAI* Crohn’s Disease Activity Index, *CBC* complete blood count, *CMP* comprehensive metabolic panel

### Who will take informed consent? {26a}

All possible efforts will be taken to maintain the privacy of participant information throughout the trial. All study staff will be trained in and maintain up-to-date certification in Good Clinical Practices, Human Subjects Research, the Responsible Conduct of Research, and HIPAA regulations. A member of the study staff will obtain informed consent at the screening and baseline visits prior to initiating any study procedures. Telephone screening will be conducted to evaluate participant eligibility per the criteria noted in Table 2 and are assigned an alpha-numeric screening ID. Participants who remain eligible following the phone screen will be invited to an in-person clinical screening visit. Informed consent for the remainder of the trial will be obtained at the baseline visit and will cover all trial operations, including a HIPAA authorization for release of medical records, anthropometric data collection, performance of an abdominal exam, and collection of blood, urine, and stool biologic specimens, with the option for elective, de-identified specimen storage for future research.

### Additional consent provisions for collection and use of participant data and biological specimens {26b}

Collection of anthropometric and demographic data, performance of an abdominal exam, and collection of hematologic specimens by venipuncture will be conducted by a qualified study team member and stored in a de-identified manner as described above.

## Interventions

### Explanation for the choice of comparators {6b}

Participants will be randomized to either the experimental drug or placebo. An inert placebo is the appropriate comparator as this phase of research is to establish safety, and clinical efficacy is unknown. Should mechanistic data and/or participant reports suggest clinical benefit, future trials may include active comparators. The placebo contains 288 mg of rice protein, 109.3 mg microcrystalline cellulose, 4.3 mg Aerosil® 200 fumed silica, and 4.3 mg magnesium stearate encapsulated in an opaque orange gelatin capsule. Participants will be instructed to take one capsule per day, orally, with their first daily meal following randomization (Table 3). Bottles of placebo capsules will be stored in a locked cabinet prior to administration in climate-controlled conditions and monitored weekly for consistency in ambient temperature.

### Intervention description {11a}

The experimental drug will be 24 mg of 99%+ pure XN with 288 mg of rice protein, 109.3 mg microcrystalline cellulose, 4.3 mg Aerosil® 200 fumed silica, and 4.3 mg magnesium stearate encapsulated in an opaque orange gelatin capsule. Participants will be instructed to take one capsule per day, orally, with their first daily meal following randomization (Table 3). Bottles of the experimental drug will be stored in a locked cabinet prior to administration in climate-controlled conditions and monitored weekly for consistency in ambient temperature.

### Criteria for discontinuing or modifying allocated interventions {11b}

Participants may elect to withdraw from the trial at any time for any reason. Participants may be withdrawn by the study team if they experience any new-onset, moderate or severe adverse events from the intervention. Any a priori-specified critical lab value observed and confirmed on repeat analysis and attributable to the intervention may also result in participant withdrawal. The trial will be halted if >20% of all participants demonstrate laboratory abnormalities in per the criterion listed *or* experience adverse events of moderate or greater severity which are new from baseline or progressively worsening.

No modifications of intervention dose or frequency of administration are allowed, and participants will be considered non-adherent and withdrawn from the trial if deviations from the dosing standard are reported to the study team. As XN was demonstrated as safe and tolerable in healthy adults at the same dosage and length of time in our phase I study [15], and is considered Generally Recognized as Safe [20], it is not anticipated that serious harms will require early discontinuation of the product or medical intervention to address the issue.

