### Strategies to improve adherence to interventions {11c}

Adherence will be monitored throughout the trial at weekly visits through verbal query and formally assessed at the week 4 and closeout visits by capsule count. Participants will be provided with sufficient study product for 5 weeks (35 capsules) at randomization and week 4 in anticipation of potential scheduling changes and/or unexpected losses. Participants will be considered adherent by taking >80% of expected doses throughout their participation in the trial. Participants will be provided suggestions to improve adherence such as daily phone alarms, consistent timing, reminder notes, etc. Returned study product will be stored in a locked cabinet in a locked room for future quality assessment.

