### Provisions for post-trial care {30}

Participants will be contacted to determine the progression and resolution of any new-onset symptoms that appear following the baseline visit. The study team will send reports of any grade 3 or higher adverse events to the participant’s medical provider(s) following their participation in the trial.

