The primary endpoint for laboratory values and vital sign measurements will be mean change from baseline to week 8, with changes also compared between groups from baseline to each additional follow-up visit (i.e., 2, 4, and 6 weeks). The frequency of new-onset or worsening laboratory values will be reported within groups throughout the trial at each biweekly visit. AEs and event severity will be reported as new-onset or worsening events spontaneously and at each biweekly visit. Together, these outcomes will provide a profile of safety and tolerability of 24mg XN for 8 weeks compared to placebo.

Secondary and exploratory outcomes include clinical disease activity, systemic inflammation (e.g., IL-10), intestinal permeability (e.g., intestinal fatty acid binding protein) and endotoxemia (e.g., LPS), platelet function, stool microbiome and bile acid composition, and the metabolic profile of XN in humans over 8 weeks. Each measurement will be collected at every biweekly clinical visit and compared between groups as mean change from baseline within groups and compared between groups at each follow-up visit. The primary endpoint for each secondary and exploratory outcome will be considered exploratory and reported as mean change within groups at week 8 from to baseline and compared between groups at each follow-up visit. The measurements to support these outcomes are outlined in Table 1.

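### A reported dosing deviation can end a participant's safety follow-up, not just study product, and the per-protocol analysis can then leave poor tolerators out of the primary comparison

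*Protocol article*

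**What the plan says.** Section {11a} sets the regimen: "Participants will be instructed to take one capsule per day, orally, with their first daily meal following randomization". Section {11b} then states "No modifications of intervention dose or frequency of administration are allowed", and in the same sentence that "participants will be considered non-adherent and withdrawn from the trial if deviations from the dosing standard are reported to the study team". It gives no number of missed doses and no exception for side effects, and it does not define the dosing standard. Earlier in that section, withdrawal for harm is discretionary: "Participants may be withdrawn by the study team if they experience any new-onset, moderate or severe adverse events from the intervention".

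Section {11c} defines adherence differently: "Participants will be considered adherent by taking >80% of expected doses throughout their participation in the trial". Staff ask about adherence at visits and count capsules at week 4 and closeout. The section also provides coaching: "Participants will be provided suggestions to improve adherence such as daily phone alarms".

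On outcomes, section {12} says "The primary endpoint for laboratory values and vital sign measurements will be mean change from baseline to week 8". Adverse events are also a primary outcome. Section {20c} puts all analyses on a per-protocol basis and cites the trial's safety orientation as the reason. Its one sensitivity analysis multiply imputes missing laboratory data.

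**The concern.** The trial's main question is safety and tolerability. Skipping capsules because they cause symptoms is itself a sign of poor tolerability. A rule that answers it by ending trial participation links loss of data to the outcome under study, and an analysis restricted to protocol adherers adds to the problem. If XN is less well tolerated than placebo, more XN participants would be lost this way, and the comparison would move towards the hypothesis that XN is safe.

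The wording also sets an odd priority. A participant with a moderate adverse event who keeps taking capsules may stay. On the literal reading, one who skips a few doses for a milder event must go.

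**Working it through.** **Inputs.** One capsule a day for 8 weeks gives 56 expected doses ({11a}). The adherence threshold is above 80% ({11c}). Follow-up visits are at weeks 2, 4, 6 and 8 ({12}, {13}). The design needs 12 per arm, allows 25% attrition and randomises up to 32; phase I attrition was 10% ({14}). The stipend is $50 for screening and $190 per later visit, to a maximum of $1000 ({18b}).

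**The plan's own figure.** 12 / (1 − 0.25) = 16 per arm, or 32 in total. This reproduces.

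**Where the two adherence rules meet.**
- 45/56 = 80.4% (adherent) and 44/56 = 78.6% (not adherent), so up to 11 misses are allowed over the trial.
- At the week 4 count, 23/28 = 82.1% and 22/28 = 78.6%, so up to 5 misses are allowed.
- A participant who skips 3 doses and resumes finishes at 53/56 = 94.6%.

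**Three readings of {11b}.**
1. Literal: any reported deviation leads to withdrawal. The participant at 94.6% is adherent under {11c} but withdrawn under {11b}. The rules conflict for 1 to 11 reported misses.
2. Regimen change: only a deliberate change of dose or frequency counts. Forgotten capsules then cause no conflict. Whether three skipped doses amount to a change of frequency is open.
3. Threshold: a deviation matters only once adherence is no longer above 80%. The participant at 94.6% stays; one who skips 12 doses (78.6%) does not.

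Under all three, someone who skips doses because of side effects can be withdrawn, and what ends is trial participation rather than study product alone.

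**Visits lost.** Withdrawal before week 2 loses 4 of 4 follow-up visits. Withdrawal at the week 2, 4 or 6 visit loses 3, 2 or 1. Skipping first reported at closeout loses none. The week 8 value is lost in every case except the last.

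**Effect of omitting one participant with an event.** If k of n in an arm had events, the rate falls by k/n − (k − 1)/(n − 1) = (n − k) / (n(n − 1)).
- n = 12, k = 1: 11/132 = 8.3 points
- n = 12, k = 3: 9/132 = 6.8 points
- n = 12, k = 6: 6/132 = 4.5 points
- n = 12, k = 11: 1/132 = 0.8 points
- n = 16: from 15/240 = 6.25 points (k = 1) to 1/240 = 0.4 points (k = 15)

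This applies only if that participant's events are left out of the per-protocol set. The same arithmetic holds in either arm.

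**Effect on numbers.** If 32 are randomised and 10% attrition recurs, 32 × 0.9 = 28.8 remain. Four further withdrawals leave 24.8. Five leave 23.8, below the 24 needed. This assumes that the 10% excludes dosing withdrawals, which the article does not say.

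**The case against.** The strongest reply is that the conflict depends on interpretation. The dosing standard is undefined. {11b} removes people considered non-adherent, and the next section says who is considered adherent. Coaching and capsule counts would serve little purpose if one reported miss ended participation. This stands. A reader might infer that everyone who skips doses for side effects must leave even while above 80%; the text permits that reading but does not require it.

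A second reply is that the data loss is smaller than it looks. Skipping first reported at closeout costs no visit. Group changes are also compared at weeks 2, 4 and 6, and laboratory trends use a repeated-measures model, so earlier visits could still contribute. Adverse events are graded up to withdrawal. Section {30} adds that "Participants will be contacted to determine the progression and resolution of any new-onset symptoms that appear following the baseline visit". Retention and adherence are themselves tolerability measures ({18a}). All of this stands as partial mitigation. None of it supplies week 8 laboratory values or vital signs for a participant withdrawn earlier.

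A third reply is that the make-up of the per-protocol set and visits after withdrawal may be settled in documents not shown. For the analysis set this is fair: whether withdrawn participants' earlier events are counted is not stated here, and an analysis plan can decide it. But such a plan cannot recover visits that were not held, and the article's withdrawal rule ends trial participation rather than product alone.

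Finally, the size is hypothetical. The article gives no rate of dose skipping and no count of withdrawals under this clause, and the design already allows for 8 of 32 to be lost. This also stands.

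**Conclusion.** The concern holds in a limited form and should be fixed. Section {11b} is worded so that it can contradict the adherence rule in {11c}. On any reading, it can end follow-up for participants who skip doses because they tolerate the product poorly. Combined with a per-protocol analysis of the primary safety outcomes, this can remove them from the comparison that the trial exists to make. Vital signs, adverse events and PROMIS-29 have no sensitivity analysis for the loss.

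The size is unknown. The 0.8 to 8.3 point figure per omitted participant (12 per arm) assumes that the participant had an event and that it is dropped from the analysis. A reader might infer that the rule biases the trial towards finding XN safe. The documents do not show that: the direction depends on which arm loses more participants, allocation is blinded, and no withdrawals by arm are reported. If only deliberate changes count, forgotten capsules add no attrition. Confidence is moderate.

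**What to change.** - Reword {11b} so that a deliberate change of dose or frequency stops study product only, and state that scheduled visits continue to week 8.
- Make above 80% of expected doses by capsule count the single adherence rule for the per-protocol set.
- Analyse safety and tolerability primarily in all randomised participants who took at least one dose, by randomised arm, with per protocol as supporting.
- List anyone already withdrawn under this clause by arm, with the reason, once the trial is unblinded.

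**Cost.** This needs an amendment with IRB approval and, where required, submission to NCCIH and the FDA. Each visit kept carries its planned stipend: 1 to 4 visits × $190 = $190 to $760 per participant retained. That is within the existing cap, since $50 + 5 × $190 = $1000. With 15 of up to 32 completed at the stated status date, the follow-up change can reach up to 32 − 15 = 17 participants; the analysis change covers everyone. Changing the primary analysis population mid-trial is more than a wording edit, but the protocol keeps trial staff blinded until the primary analyses are complete, so it can still be made blind to results by arm. The statistical downside is some dilution of the exposure contrast, which the supporting per-protocol analysis addresses.

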### Strategies to improve adherence to interventions {11c}

Adherence will be monitored throughout the trial at weekly visits through verbal query and formally assessed at the week 4 and closeout visits by capsule count. Participants will be provided with sufficient study product for 5 weeks (35 capsules) at randomization and week 4 in anticipation of potential scheduling changes and/or unexpected losses. Participants will be considered adherent by taking >80% of expected doses throughout their participation in the trial. Participants will be provided suggestions to improve adherence such as daily phone alarms, consistent timing, reminder notes, etc. Returned study product will be stored in a locked cabinet in a locked room for future quality assessment.

### Relevant concomitant care permitted or prohibited during the trial {11d}

Allowable concomitant interventions are outlined according to the criteria in Table 2. Participants will be allowed rescue steroid medications for inflammatory flares associated with CD, although over-the-counter non-steroidal anti-inflammatory medications will be limited to no more than once per week.

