## Statistical methods

### Statistical method outcomes {20a}

Laboratory measures will be analyzed first with descriptive statistics including mean, median, and standard deviation. Distributions will be tested for skew and transformed (e.g., natural log) as needed to reduce skew on subsequent analyses. If distributions indicate substantial non-normality that cannot be modified with transformation, non-parametric tests (e.g., Wilcoxon rank-sum) will be used.

In addition, the frequency of new, clinically significant laboratory abnormal values as outlined above will be monitored by the DSMB. The percentage of these new abnormal values per reference ranges will be reported at each time point and compared between groups by Fisher’s exact test. Assessment for changes in the distribution of each parameter will be presented as means and confidence intervals (CI) within and between groups. The significance of differences will be compared using 2-sided, unpaired *t*-tests if normally distributed and a non-parametric Wilcoxon rank-sum test of mean values between groups if non-normally distributed. Overall increases and decreases in laboratory parameters will be tested using linear mixed ANOVA with time point as a repeated factor, potentially suggestive of cumulative toxicity if trending in a clinically deleterious direction. All factors will be considered significant if *p* < .05.

Clinical activity will be measured through the CDAI. A score >150 is considered *clinically active* and is an eligibility criterion. Changes in score from baseline between groups will be compared within groups using two-sided, unpaired *t*-tests at each interval with the primary outcome as a change in value from baseline to closeout, whereas within-group changes will be compared using two-sided, paired *t*-tests. Non-parametric Wilcoxon rank-sum test of mean values between groups will be used if data are non-normally distributed.

Measures within the PROMIS-29 v.2.0 questionnaire include seven validated subscales, i.e., physical function, anxiety, depression, pain intensity, pain interference, sleep disturbance, and social interaction. Analyses will be performed by calculating descriptive statistics of mean, median, and mode of reported *T*-scores and overall PROMIS-29 questionnaire and each subscale. Welch’s *t*-test will be used to test the differences in scores between groups with *p* < .05 considered significant.

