As this study will have a relatively small sample size, changes in secondary and tertiary outcome values will be considered preliminary but will be compared to results found in the phase I trial. Assessments for these outcomes, including inflammatory cytokines, gut permeability biomarkers, markers of endotoxemia, bile acids, and platelet function, will be calculated using Cohen’s *d* statistic for effect size and qualitatively compared for differences between trials using changes in values between baseline and closeout. The primary effect estimate will be for changes between baseline and closeout. This study is powered to detect a difference in Cohen’s *d* value of at least 1.2 between groups. Results will be considered evidence of a possible effect if a Cohen’s *d* value > 0.5 is observed. Statistical comparisons for significance will be considered exploratory and will be limited to unpaired *t*-tests between XN treatment groups.

The metabolite profiles and impact of XN on gut microbial composition and platelet function will be conducted with specific methods previously described by partner sites [31, 33]. Correlations between changes in CDAI and microbiota changes, inflammatory biomarker changes, and/or bile acid changes will be considered exploratory.

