### Methods for additional analyses {20b}

Currently, no subgroup analyses are planned. If significant differences in CDAI scores are observed between groups at baseline, ANCOVA will be performed for all tests of mean differences (e.g., circulating inflammatory cytokines), adjusting for baseline CDAI scores between groups.

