### Methods in analysis to handle protocol non-adherence and any statistical methods to handle missing data {20c}

Given the safety-oriented and mechanistic nature of the trial, all analyses will be conducted per protocol; however, as a sensitivity analysis, missing laboratory data will be imputed by multiple imputation to assess the robustness of study results.

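### Rescue steroids are allowed for Crohn's flares, but the closeout comparisons of CDAI and inflammatory markers do not separate values measured after rescue

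*Protocol article*

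**What the plan says.** All references are to the protocol article.

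- **Rescue.** Relevant concomitant care {11d}: "Participants will be allowed rescue steroid medications for inflammatory flares associated with CD". The sentence before it refers to Table 2 for allowable concomitant care. Table 2 (Eligibility criteria {10}) lists as an exclusion "Variable dosing of anti-inflammatory medications >1×/week", and also medication starts or changes in the last 14 days.
- **CDAI.** Statistical method outcomes {20a} uses t-tests, or a Wilcoxon test if the data are non-normal, "with the primary outcome as a change in value from baseline to closeout".
- **Inflammatory and other secondary markers.** The same section: "The primary effect estimate will be for changes between baseline and closeout". Outcomes {12} applies week-8 change to every secondary and exploratory outcome, and Table 1 places fecal calprotectin among these.
- **Laboratory values and vital signs.** Outcomes {12}: "The primary endpoint for laboratory values and vital sign measurements will be mean change from baseline to week 8".
- **Population and sensitivity analysis.** Section {20c}: "Given the safety-oriented and mechanistic nature of the trial, all analyses will be conducted per protocol". The one sensitivity analysis is that "missing laboratory data will be imputed by multiple imputation to assess the robustness of study results".
- **Adjustment.** Methods for additional analyses {20b} provides ANCOVA only after a baseline imbalance, "adjusting for baseline CDAI scores between groups".

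**The concern.** The protocol foresees steroid rescue. It then fixes the endpoint, the test, the population, the covariate rule and the sensitivity analysis, and none of these mentions rescue. A participant who flares, takes steroids and is better by closeout has a measured value, so imputation of missing data does not apply. If that participant stays in the analysis, the steroid-treated value can be credited to the allocated capsule.

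Rescue is a consequence of worsening, so it is not random with respect to outcome. If the placebo arm does worse and is rescued more, a real benefit of xanthohumol on CDAI or cytokines shrinks. If the xanthohumol arm is rescued more, a real disadvantage shrinks, or an apparent benefit arises where there is none. With about 12 analysed per arm, a few rescued participants can matter. These outcomes are exploratory, but they are the early efficacy signal and will be compared with the phase I trial.

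**Working it through.** **The plan's own figures.** With 12 per arm and Cohen's d = 1.2, a two-sided t-test at 0.05 has 80.2% power, which agrees with {14} and {20a}. Attrition: 24/(1 − 0.25) = 32, as stated. These figures are sound and are used only as a reference.

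**Does any stated rule catch a rescued participant?**

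1. Missing-data imputation: no, because the value is observed.
2. ANCOVA: no, because it concerns baseline CDAI only.
3. Per-protocol restriction: unclear. Rescue is permitted, so it is not by itself a deviation, and the article does not define the set. The reference to Table 2 in {11d} adds doubt, because Table 2 excludes variable anti-inflammatory dosing and recent medication changes.
4. Withdrawal under {11b}: optional, and tied to events from the intervention.

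If rescued participants stay in, their closeout values carry a steroid effect. If they are taken out, the set is selected on worsening after randomization. The article does not say which applies.

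**Size on the CDAI scale.** Shift in the contrast ≈ (rescue rate in one arm − rescue rate in the other) × steroid effect. Assumed: 3/12 versus 1/12 and 100 points. (3/12 − 1/12) × 100 = 2/12 × 100 = 16.7, about 17 points.

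**A fuller illustration, all inputs assumed.** Change on placebo is normal with mean −20 and SD 60 or 80; xanthohumol shifts it by 50 points either way; anyone with a rise above 30 is rescued; rescue lowers CDAI by 70, 100 or 150.

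- True benefit of 50: rescue about 20–27% on placebo and 5–11% on xanthohumol; observed benefit 26–39 points.
- True harm of 50: rescue about 50% on xanthohumol and 20–27% on placebo; observed harm 5–34 points.

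**Size as Cohen's d.** Observed d = true d − (placebo rate − xanthohumol rate) × steroid shift in SD, with the SD held fixed. True d = 1.2, 12 per arm, rates and shifts assumed; power in brackets:

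| Rescue, placebo vs xanthohumol | shift 0.5 SD | shift 1 SD | shift 2 SD |
|---|---|---|---|
| equal | 1.20 (80%) | 1.20 (80%) | 1.20 (80%) |
| 30% vs 10% | 1.10 (73%) | 1.00 (65%) | 0.80 (47%) |
| 40% vs 10% | 1.05 (69%) | 0.90 (56%) | 0.60 (29%) |

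**No true effect, xanthohumol rescued more (40% vs 10%).** Spurious d in favour of xanthohumol = 0.30 × 0.5, 1 or 2 = 0.15, 0.30 or 0.60. Only the last exceeds the 0.5 that {20a} treats as evidence of a possible effect.

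**The case against.** The strongest reply is that the point rests on silence. The article never says that post-rescue values are used as observed, a statistical analysis plan not shown may handle rescue, and comparing arms regardless of rescue is a legitimate choice. This stands in part. An unseen plan could add a rule, but it would have to qualify a population, endpoint and sensitivity analysis that the article already fixes.

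A reader might infer more than the documents support:

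- **That every treated flare counts as improvement.** It may not have resolved by closeout, and the participant may have left or been excluded. With equal rescue and equal steroid effect there is no net shift.
- **That the primary safety comparison is biased towards no difference.** Steroids may move laboratory values and vital signs, but nothing in the documents gives a direction; they could create a difference as well as hide one.
- **That harm would be concealed.** New or worsening adverse events are a primary outcome, recorded at each biweekly visit and spontaneously ({12}, {22}). Between-group comparisons are also planned before closeout. Under {11b} the trial halts if more than 20% of all participants have new or progressively worsening adverse events of at least moderate severity. The harm illustration above has about 35–38% of all participants rescued, so if those flares were graded moderate the trial would stop.
- **That {11d} flatly contradicts Table 2.** Table 2 is mainly a list of entry criteria, and {11d} can be read as a general rule followed by a specific allowance. What remains is the doubt about who counts as per protocol.

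These points narrow the concern. They do not supply a rule for CDAI and inflammatory values after rescue.

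**Conclusion.** The concern holds for CDAI, cytokines and fecal calprotectin. The protocol permits steroid rescue and does not say how values after it enter the closeout comparison, or whether the participant remains in the per-protocol set. Unequal rescue can shrink a true difference or mimic an effect by about the rescue-rate difference times the steroid effect. The 17-point example and the table show what plausible inputs would do; every rescue rate, steroid effect and CDAI SD in them is assumed, so they are not forecasts. For laboratory values and vital signs the supportable statement is weaker: steroid use is a confounder of unspecified direction. The documents do not support a claim that the primary safety conclusion is biased towards no difference or that harm would go unseen.

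**What to change.** Leave access to rescue as it is, and change the analysis text:

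1. Reconcile {11d} with Table 2, and state whether a participant who takes rescue steroids stays in the per-protocol set.
2. Report the number rescued in each arm as a disease-activity and tolerability result.
3. Keep the planned closeout comparison of CDAI and inflammatory markers. Beside it, add an analysis that ranks rescued participants worst, using the Wilcoxon test that {20a} already names. Rescued participants must be retained for it. For the inflammatory markers {20a} limits significance tests to unpaired t-tests, so that sentence needs a matching exception. Do not substitute the last value before rescue: with biweekly visits it can predate the flare and erase the worsening.
4. Keep post-rescue laboratory values and vital signs in the safety tables, flagged, and repeat the week-8 comparison once without them.

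The cost is a little extra analysis, with no added visits or participants; it needs the rescue information for each participant at analysis. The worst-rank result yields no mean difference or Cohen's d, which is why it should stand beside the planned comparison and not replace it.
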